## Abstract

*Background and Objectives:* The motor sequelae after a stroke are frequently persistent and cause a high degree of disability. Cortical ischemic or hemorrhagic strokes affecting the cortico-spinal pathways are known to cause a reduction of cortical excitability in the lesioned area not only for the local connectivity impairment but also due to a contralateral hemisphere inhibitory action. Non-invasive brain stimulation using high frequency repetitive magnetic transcranial stimulation (rTMS) over the lesioned hemisphere and contralateral cortical inhibition using low-frequency rTMS have been shown to increase the excitability of the lesioned hemisphere. Mental representation techniques, neurofeedback, and virtual reality have also been shown to increase cortical excitability and complement conventional rehabilitation. *Materials and Methods:* We aim to carry out a single-blind, randomized, controlled trial aiming to study the efficacy of immersive multimodal Brain–Computer Interfacing-Virtual Reality (BCI-VR) training after bilateral neuromodulation with rTMS on upper limb motor recovery after subacute stroke (>3 months) compared to neuromodulation combined with conventional motor imagery tasks. This study will include 42 subjects in a randomized controlled trial design. The main expected outcomes are changes in the Motricity Index of the Arm (MI), dynamometry of the upper limb, score according to Fugl-Meyer for upper limb (FMA-UE), and changes in the Stroke Impact Scale (SIS). The evaluation will be carried out before the intervention, after each intervention and 15 days after the last session. *Conclusions:* This trial will show the additive value of VR immersive motor imagery as an adjuvant therapy combined with a known effective neuromodulation approach opening new perspectives for clinical rehabilitation protocols.

## 1. Introduction

Stroke is a leading cause of long-term disability; it reduces mobility in more than half of stroke survivors age 65 and over [1].

Despite the lack of objective prognostic factors regarding the patient’s functionality after a stroke, we know that age, the level of initial disability, and the location and size of the lesion are elements that affect the evolution of post-stroke rehabilitation [2].

After a stroke, the recovery of lost functions in the brain is achieved thanks to reorganizing networks in a process known as plasticity. Some damaged brain tissues may recover, or undamaged areas may take over some functions.

One of the most relevant aspects of the rehabilitation prognosis is the time of evolution. After a stroke, improvement is noticeably reduced over the second month, finding stabilization around the sixth month. One of the reasons that explain this fact is the reduction of neuroplasticity [3]. There are indicative studies that reflect that, six months after a stroke, more than 60% of subjects will have a non-functional hand for Basic Activities of Daily Living (BADL), and 20–25% will not be able to walk without assistance [4]. These impairments determine the important global burden that stroke represents [5]. It is relevant to emphasize that the degree of disability after the rehabilitation process will be determined by the combination of existing motor, sensory, and neuropsychological deficiencies [6].

In the last years, several non-invasive neuromodulation techniques have been shown efficient to enhance plasticity and stroke recovery. Among these interventions, we can find exogenous neuromodulation, meaning that the neuromodulator stimulus comes from an external source, as is the case with rTMS (repetitive transcranial magnetic stimulation), which has the capacity to change the cortical excitability depending on the frequency of the magnetic pulses. Low frequencies (≤1 Hz) reduce local neural activity, and high frequencies (≥5 Hz) increase cortical excitability [7]. This technique has been successfully used bilaterally, stimulating the injured hemisphere and inhibiting the healthy one, to treat the interhemispheric inhibition phenomenon in stroke patients as it influences stroke recovery [8]. Although up to date there are some consensus recommendations about dosing and parameters of rTMS in some clinical applications such as pain [9] and depression [10], there is no clear consensus about the recommended parameters in stroke due to the heterogeneity of the currently published studies [11].

On the other hand, there are endogenous neuromodulation techniques that depend on the capacity of the subject to modulate its own brain activity. This can be achieved using neurofeedback (NFB), which consists of recording information of brain activity using electroencephalography (EEG) or functional magnetic resonance (fMRI) and displaying it to the subject in such a way that he can receive real-time information of his own brain function. Virtual reality allows a new dimension on the neurofeedback immersion and is likely to increase its efficacy [12]. Stroke patients have been trained to reinforce certain EEG rhythms related to motor performance using the NFB technique showing favourable effects on rehabilitation outcomes [13].

Some other techniques aiming to increase brain plasticity use the practice of imagination of movement of the affected hemibody [14]. This is known as motor imagery [15] and can also be enhanced through the use of brain–computer interfaces [16]. All the neuromodulation techniques are used to complement but not as a replacement of conventional rehabilitation [17,18].

On the one hand, exogenous neuromodulation effects are produced mainly by changes directly induced in cortical excitability [19], and on the other hand, endogenous neuromodulation is believed to have more widespread subcortical effects [20,21]. Currently, the exact mechanisms underlying motor recovery using neuromodulation techniques are still being investigated. Simultaneous activation of inputs and outputs to cortical motor areas is believed to trigger Hebbian plasticity, which strengthens cortical-subcortical connectivity. Improvements in this cortical-subcortical connectivity have been linked to better motor recovery after stroke [22,23].

One of the probable causes of the short-term effects of these techniques is the ceiling effect of changes in cortical excitability that can be achieved non-invasively, but despite the good results achieved with the use of non-invasive neuromodulation techniques individually, there is a shortage of validated neurorehabilitation protocols that integrate different approaches that have been proven to be effective individually.

It has been suggested rTMS may be a good conditioning method whose effect would be to increase brain plasticity that would improve the results of subsequent rehabilitation [24]. There are already several studies that compare rTMS alone with its combination with motor rehabilitation showing good results when rTMS is used as a primer that may help to reach a greater cortical activation and boosting plasticity [8,25,26,27]. Motor imagery and action observation have been shown to effectively activate the same brain areas as an actual movement [28]; up to date, it has not been combined with rTMS.

There is increasing evidence of Brain–Computer Interfacing (BCI) efficacy as rehabilitation technology in patients with severe motor impairments [29]. This is the case with NeuRow [30]. It is an immersive multimodal Brain–Computer Interfacing (BCI) training paradigm that combines motor imagery and embodied neurofeedback using virtual reality. NeuRow has been designed to be used by the chronic stroke patient population [31], and its efficacy has been shown in a pilot study. It shows clear improvements and recovery regarding motor function in terms of clinical scales (FMA, MAS, SIS), self-reported scales, electrophysiological data, and brain imaging data (fMRI). There is evidence that BCI-based rehabilitation promotes lasting improvements in motor function in chronic stroke patients with hemiparesis [32].

Both approaches, the NeuRow training paradigm (NeuroRehabLab, Funchal, Portugal) and bilateral rTMS protocols, are likely to complement their effects, achieving a stronger neuroplasticity enhancement in stroke patients. Both have been used separately for the treatment of motor sequelae in the upper limbs after stroke [8,31,33]. The effects of these combined techniques are not likely to be based only on the increase of cortical excitability but also on subcortical mechanisms.

The efficacy of rTMS and motor imagery has been previously demonstrated, but their combination has not been tested yet. The main objective of this study is to carry out a double-blind, randomized, controlled trial aiming to study the clinical effect of immersive multimodal BCI-VR training using NeuRow system (NeuroRehabLab, Funchal, Portugal) after bilateral neuromodulation with rTMS compared to bilateral rTMS plus conventional rehabilitation in upper limb motor sequelae after subacute stroke (>3 months). We will look for changes in: 1. isometric strength in the upper limb; 2. functional motor scales of the upper limb; 3. hand dexterity; and 4. cortical excitability changes. Our main hypothesis is that multimodal BCI-VR training will be superior to the use of conventional motor imagery as adjuvant therapy to bilateral rTMS.

This protocol combines techniques that have proven to be cost-effective [34]. If it is shown that the clinical improvement with this combination is significant, it will open a new line of combined neuromodulation approaches to reach an effective method for the upper limb motor neurorehabilitation after a stroke.

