### 2.1. Study Design and Participants

Participants will be recruited in the Brain Injury Unit or Rehabilitation Unit of the Beata María Ana Hospital; patients referred from other centres and self-referred patients will also be considered. The subjects included will be assessed by a neurologist ([name]) and a physiotherapist ([name]). All patients will have had a hemispheric ischemic or hemorrhagic stroke (>3 months after stroke) diagnosed in at least one brain-imaging test and presenting motor sequelae in the upper limb. We have ruled out the first three months since the phenomenon is known as “spontaneous recovery” [36] takes place in time, and therefore, it would be difficult to discern the cause of the clinical improvement that we expect from patients. The patients included in the study will have an alteration of mobility and/or functionality in the upper limb related to the stroke and with a score equal to or greater than 25 according to the Fugl-Meyer Assessment for upper extremity (FMA-UE) [37]. The rest of the specific inclusion and exclusion criteria are shown in Table 1.

The study design corresponds to a randomized, single-blind, controlled clinical trial in which patients are randomly assigned to two groups: 1. Conventional rehabilitation + bilateral rTMS + Immersive multimodal BCI-VR training system NeuRow (NeuroRehabLab, Funchal, Portugal), and 2. Conventional rehabilitation + bilateral rTMS.

Regarding adherence strategies, sessions missed up to the established limit will be restored the following week. Flexible therapy schedules will also be offered, and patients’ families will be contacted directly by phone to confirm evaluation dates, thus reinforcing treatment adherence [38].

To calculate the sample size, the GRANMO calculator was used *(Sample size and power calculator (v. 7.12.), Institut Municipal d’Investigació Mèdica, Barcelona, Spain)*. Accepting an alpha risk of 0.005 and a beta risk of 0.2 in a one-sided contrast, 23 subjects are required to detect a difference equal to 4.9 points, the minimal clinically important difference of the Fugl-Meyer assessment scores for wrist/hand [39]. Considering a 15% loss, it will be necessary to reach a sample of 21 patients in each group.

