### 2.2. Intervention Protocol

The two intervention protocols have been extracted from previous publications of successful application on upper limb rehabilitation. On the one hand, the investigation by Takeuchi et al. showed significant improvements in those subjects who received bilateral rTMS stimulation (based on the principle of interhemispheric inhibition) [8]. On the other hand, Vourvopoulos et al. published a pilot study using NeuRow, showing a high performance [33].

The intervention will consist of the two therapies administered sequentially on the same day rTMS application before the immersive multimodal BCI-VR training, or just rTMS application, in the control group. The sequence of administration has been decided based on preliminary results of the NeuroMOD project (unpublished) from our group, revealing that patients receiving rTMS prior to NFB had a better performance.

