#### 2.2.2. Immersive Multimodal BCI-VR Training

NeuRow is a gamified BCI training paradigm in VR that allows patients to perform similar motor actions as they would do in real life. NeuRow is rendered through a head-mounted VR headset with 90° horizontal field-of-view and haptic feedback delivered through 2 controllers in both hands.

The paretic limb should be positioned in a resting position on the table. Before setting up the EEG cap plus VR headset in each session, a previous training will be carried out with the following instructions:Ask the patient to perform the rowing movement with both upper limbs with external facilitation of the paretic side.Ask the patient to imagine the movement with eyes closed, focusing on his internal perspective and on the sensation of rotation. Imagine the hand closed in a fist and feel the arm weight and contraction of arm muscles.Imagine the movement slowly and increase their speed.The best strategies will be identified for each participant. The patient reports in detail what he felt/tried to visualize; the researcher will give feedback and will also give a description of the sensation of the movement to the participant during the motor imagination, describing the sequence of movements required for rowing (elbow stretched, closed hand grasping the paddle, etc.).The patient will be asked if he succeeds in imagining the tasks.

It is very important that the movement is natural and biomechanically correct. This training will be carried out daily and prior to the application of the NeuRow system.

Before the actual VR training, the acquisition of the EEG will be carried out. An experienced technician will acquire EEG through a BCIs system with 64 active electrodes equipped with a low-noise biosignal amplifier and a 24 bit A/D converter at 256 Hz (BrainVision actiCHamp biosignal amplifier, Brain Products GmbH, Gilching, Germany). The spatial distribution of the electrodes will cover primarily the motor and somatosensory areas of the brain. Specifically, the Frontal (F3, Fz, F4), Frontal-Central (FC5, FC6), Central (C3, Cz, C4), Central-Parietal (CP5, CP1, CP2, CP6), and Parietal (P3, Pz, P4) in a small Laplacian configuration for spatial filtering (Figure 1). EEG data acquisition and processing will be performed through the OpenVibe platform [42], which will transmit the data via the Lab Streaming Layer (LSL) protocol to control the virtual environment.

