## 4. Conclusions

This trial will show the additive value of VR immersive motor imagery as an adjuvant therapy combined with a known effective neuromodulation approach opening new perspectives for clinical rehabilitation protocols. This therapy could potentially reduce the time required for hand rehabilitation or improve functional outcomes reducing long-term disability.

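### The article names two different comparators: with the arms set out in Methods it tests NeuRow as an add-on, not BCI-VR against conventional motor imagery, and its double-blind label is contradicted elsewhere

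*Protocol article*

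**What the plan says.** Two places name motor imagery as the comparator. The Abstract describes BCI-VR training after rTMS "compared to neuromodulation combined with conventional motor imagery tasks". The main hypothesis in the Introduction is that "multimodal BCI-VR training will be superior to the use of conventional motor imagery as adjuvant therapy to bilateral rTMS".

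Four places describe something else:

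- The main objective, in the same paragraph as the hypothesis, has BCI-VR after rTMS "compared to bilateral rTMS plus conventional rehabilitation in upper limb motor sequelae".
- Section 2.1 defines arm 1 as conventional rehabilitation, bilateral rTMS and NeuRow, and arm 2 as the first two of these without NeuRow.
- Section 2.2 describes rTMS followed by BCI-VR, "or just rTMS application, in the control group".
- The Figure 2 legend lists 10 rTMS sessions for controls, and 10 rTMS plus 12 NeuRow sessions for the experimental arm.

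Section 2.2.2 adds preparation before each NeuRow session. Patients are asked to "perform the rowing movement with both upper limbs with external facilitation of the paretic side", and are then coached in imagining the movement.

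On blinding, the Introduction says "The main objective of this study is to carry out a double-blind, randomized, controlled trial". Section 2.1 says "The study design corresponds to a randomized, single-blind, controlled clinical trial in which patients are randomly assigned to two groups", and the Abstract also says single-blind. Section 2.1 describes as blind the researcher who generates the sequence, the staff member who assigns patients, and the evaluators.

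**The concern.** The comparator determines what the trial estimates and what a positive result may be said to show. A reader of the hypothesis expects a head-to-head comparison of two adjuncts to rTMS. A reader of Methods sees one adjunct compared with none. If the trial runs as Methods describes and is reported under the hypothesis, it would claim superiority over a treatment that no control patient is described as receiving.

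This matters more because the Introduction itself regards the efficacy of motor imagery as already shown. On the authors' own account, the imagery coaching given with NeuRow could produce a between-arm difference without any contribution from BCI-VR.

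The blinding label affects how much protection readers assume for effort-dependent outcomes such as maximal grip strength, one of the main outcomes.

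**Working it through.** The article gives no figure to reproduce here. The check sets the texts side by side and counts sessions.

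**1. Comparator by location**

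| Location | Control condition |
|---|---|
| Abstract | rTMS + conventional motor imagery |
| Introduction, hypothesis | rTMS + conventional motor imagery |
| Introduction, objective | rTMS + conventional rehabilitation |
| Section 2.1, arm 2 | rTMS + conventional rehabilitation |
| Section 2.2 | rTMS only |
| Figure 2 legend | 10 rTMS sessions |

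The two versions cannot both be right. Every operative description of the arms falls in the second group.

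**2. Study sessions per arm (Figure 2 legend)**

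- Control: 10.
- Experimental: 10 + 12 = 22.

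**3. Scheduled NeuRow time (section 2.2.2: 12 sessions of 30 min, each with 3 series of 7 min)**

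- Scheduled: 12 × 30 = 360 min = 6 h. The article says the 30 min include initial training and breaks.
- Training series alone: 12 × 3 × 7 = 252 min.

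No counterpart to these 12 sessions is described for controls.

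**4. What the Methods arms identify**

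As a simple additive sketch, write T for rTMS, C for conventional rehabilitation, R for assisted rowing, M for imagery coaching, B for BCI-VR, and A for the additional session time.

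- Experimental arm: T + C + R + M + B + A
- Control arm: T + C
- Difference: R + M + B + A

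The hypothesis concerns B relative to conventional imagery. One observed difference cannot separate four terms, and interactions would only add unknowns. No analysis plan for these two arms could recover the hypothesised contrast.

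**5. Could imagery sit inside conventional rehabilitation?** Section 2.1 gives conventional rehabilitation to both arms. Any imagery within it would be common to both, and the difference would still be the added NeuRow package rather than BCI-VR against imagery.

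**6. Blinding.** One location says double-blind and two say single-blind. The masked roles described are the evaluators and the randomisation and allocation staff. Participants and those delivering treatment are not among them, and one arm trains with an EEG cap and VR headset while no sham or parallel session is described for the other.

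**The case against.** Several points on the other side stand.

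- **The control arm is contradictory, not settled.** A reader might infer that controls definitely receive no imagery and that the trial cannot test its hypothesis. The documents do not support that outright: the Abstract gives controls imagery tasks, and Table 1 requires a minimum imagery score of all participants, which fits an imagery comparator without proving one. The content of conventional rehabilitation is also not described, and a condensed article may leave it to the full protocol. The conclusion is therefore conditional on the Methods arms being the operative ones.
- **An add-on design without matched sessions is legitimate.** The absence of sham or attention-matched sessions is not an error. The fault lies in describing a different contrast.
- **The Conclusions section is not at fault.** "This trial will show the additive value of VR immersive motor imagery as an adjuvant therapy" can be read as the add-on question, and the Discussion likewise presents BCI-VR as an enhancer of rTMS. It needs only to avoid being taken as a VR-specific effect.
- **The 6 hours are not a net contact difference.** They are scheduled NeuRow time. The article does not call the sessions one-to-one, and it does not state the amount or timing of conventional rehabilitation in either arm.
- **The Stroke Impact Scale is not described as patient-reported.** The Introduction lists it among clinical scales, apart from self-reported ones, and evaluators are masked. No claim of bias specific to that scale is made here.

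One might also calculate the power lost against an active imagery control. That needs a standard deviation and the share of effect due to imagery. The article gives neither, so this point does not rely on such a figure.

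**Conclusion.** The article contradicts itself on the comparator, and this must be resolved because the main question is otherwise undefined. Assuming the arms in section 2.1, section 2.2 and the Figure 2 legend are the real ones, the trial estimates the whole NeuRow package added to rTMS and rehabilitation against rTMS and rehabilitation alone. The arms then differ by 12 study sessions (22 against 10), or 6 scheduled hours including breaks. Superiority of BCI-VR over conventional motor imagery, or an effect specific to VR, could not be concluded from that comparison.

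The double-blind label is contradicted by the Abstract and section 2.1 and is not supported by the masking described. Evaluator blinding remains feasible. Taken alone, the label is an editorial correction and adds little to the seriousness of the comparator problem.

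**What to change.** State one comparator consistently in the Abstract, the objective and hypothesis in the Introduction, sections 2.1 and 2.2, and the Figure 2 legend.

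- **If the Methods arms are the real ones:** restate the Abstract comparator and the hypothesis as the add-on contrast. For example: *the NeuRow package (assisted rowing, coached motor imagery and BCI-VR) added to bilateral rTMS and conventional rehabilitation is superior to bilateral rTMS and conventional rehabilitation alone.* Make no claim of superiority over conventional motor imagery or of a VR-specific effect. The Conclusions can stay if they are read in that sense.
- **If motor imagery is the real comparator:** the objective, sections 2.1 and 2.2, and the Figure 2 legend must be reconciled with the Abstract and hypothesis.

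In both cases, replace double-blind in the Introduction with single-blind (evaluator).

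The first route costs only wording, and its downside is a narrower headline claim. The second requires the control arm to be described afresh wherever the arms are defined.
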